#### Time point “T0”—receiving the first pair of orthopedic shoes (baseline)

Two to 3 months after the multidisciplinary consultation, the participant will receive their first pair of orthopedic shoes during a consultation with the pedorthist. A temperature microsensor (Orthotimer®) is embedded in the insole of the orthopedic shoes for determining adherence by measuring and recording wearing time.

#### Time point “T1”—shoe control after receiving the first pair of orthopedic shoes

The participants will have another consultation with the pedorthist (2 to 4 weeks later) for shoe control and fitting the second pair of orthopedic shoes. During this consultation, they receive an activity monitor and instructions from the investigator. The participants will be instructed to wear the activity monitor (Misfit Shine 2™) for a whole week starting the day after this consultation (24 h per day).

Six months after the first consultation with the podiatrist, most participants will have another regular consultation with the podiatrist for foot care. If the podiatrist is MI-trained also in this consult, MI will be applied.

#### Time point “T2”—receiving the second pair of orthopedic shoes

To deliver the second pair of orthopedic shoes, a regular consultation will be made with the pedorthist 3 months after receiving the first pair of shoes. The second pair of shoes will also be provided with a temperature microsensor (Orthotimer® microsensor) embedded in the insole of the orthopedic shoes. During this consult, the temperature microsensor of the first pair of shoes will be read out with the reading device (Orthotimer® readerdevice) by the investigator.

#### Time point “T3”—shoe control after receiving the second pair of orthopedic shoes

Two to 4 weeks after receiving the second pair of orthopedic shoes, another regular control consultation will be planned. Again, the patients will receive an activity monitor to register their activities. The activity monitor (Misfit Shine 2™) will also be worn again for one whole week (24 h per day).

#### Time point “T4”—consultation with the investigator

Three months after receiving the second pair of orthopedic shoes, a consultation with the investigator will be made to read out the temperature microsensors of both pairs of shoes. The participants will also be asked to fill in some questionnaires (time point “T4” Table 2). The same 30 participants as before will be approached for a second in-depth interview about their perspective about and experiences with orthopedic shoes, and the other participants will be asked to fill in the MOS instead.

#### Time point “T5”—consultation with the podiatrist

One year after the first consultation with the podiatrist, every participant will have a regular consultation with the podiatrist for control of their feet. During this consult, the temperature microsensors of both pairs of shoes will be read out by the investigator. And also as before, in the consultations with a MI-trained podiatrist, MI will be applied.

#### Time point “T6”—close out

A last consult with the investigator will be planned about 6 months after receiving the second pair of orthopedic shoes to read the temperature microsensors out both pairs of shoes and to fill in some questionnaires (time point “T6” Table 2).

### Sample size {14}

In this study, 220 eligible participants will be required (110 in both arms), accounting for potential dropouts. Given that MI has been found to increase adherence to orthopedic shoes at home after 3 months from 31% (without MI) to 40% (with MI) [11], we conservatively anticipate that the MI provided by the podiatrists will improve adherence by at least 10%. Moreover, we estimate the use of a digital shoe-fitting procedure by the pedorthist rather than a casting-based shoe-fitting procedure to increase adherence with at least another 10%, due to the experienced improvement of last accuracy and orthopedic shoe-fitting.

Based on the observed 3 months adherence of 59% for the usual care procedure [11], we expect the 1-year overall adherence to drop to 40% for the usual care, and to be 40% + 10% + 10% = 60% for the novel care approach including the MI. Adherence often decreases over a longer term as shown in the study of Keukenkamp et al.: over time the improved adherence returned to baseline levels [11].

The sample size calculation is performed using the “clusterPower” package in R, based on a two-sided alpha of 0.05, power of 0.80, and intraclass correlation of 0.01 of patients within podiatrists. This demonstrated that this effect in a generalized linear mixed model would require 200 participants in total. Recognizing loss to follow-up, which occurred in 6 + 4 = 10 out of 85 + 86 = 171 participants in a recent study in this context [13], that is ~ 6%, we conservatively aim to include 220 participants in total.

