## Introduction

### Background and rationale {6a}

Diabetes mellitus is one of the most common chronic diseases worldwide. The disease currently affects 425 million adults worldwide [1], and this number is expected to increase to 600 million people by 2035, due to population growth and aging [2]. A significant number of people with diabetes have foot ulcers (lifetime prevalence of 19–34%) leading to foot infection, amputation, and hospitalization [3]; immobility; and reduced quality of life [4]. In addition, diabetic foot ulcers account for high costs due to unemployment (loss of productivity) and social isolation, healthcare-related costs due to treatment, hospital admissions, and home care [3, 5–9]. Therefore, prevention of foot ulcers has high priority [3–9].

Early detection of risks, self-management, and protective footwear such as orthopedic shoes are considered essential to prevent re-ulceration [10, 11]. Adherence is crucial because patients who adhere to these strategies have significantly better outcomes than those who do not [12]. However, a randomized trial in The Netherlands found that adherence to orthopedic shoes is rather low, with only 46–49% of patients wearing their orthopedic shoes for at least 80% of daily total steps [13, 14]. Research into interventions to improve this adherence is scarce [15], but the explorative study by Keukenkamp et al. [11] showed that motivational interviewing (MI) has short-term positive effects on adherence. Motivational interviewing increased adherence to orthopedic shoes at home after 3 months from 31% (without MI) to 40% (with MI) indicating the beneficial consequences of this communication method [11]. Well-powered high-quality randomized trials are needed to better inform clinical practice about different methods to improve adherence to wearing orthopedic shoes [11, 12, 16].

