#### Proportion participants being adherent

The main study parameter is the proportion of participants who adhere to wearing their orthopedic shoes, defined as minimally 80% of steps taken with orthopedic shoes. The level of adherence (see the “Level of adherence to orthopedic shoes” section) will be based on log data from temperature microsensors in the orthopedic shoes and data from the activity monitors provided to all participants over two 1-week periods measured at time point “T1” and time point “T3” (Table 2). The proportion of adherent participants will be objectively determined based on the combined level of adherence of the two measurements (the mean of time point “T1” and time-point “T3”).

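### The MI half of the assumed 20-point effect is a 9-point gain measured at home, rounded up to 10, called conservative and carried unchanged into a 1-year overall contrast

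*Protocol article*

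**What the plan says.** All the effect inputs are in the protocol article, Sample size {14}.

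- **MI gain, source:** "MI has been found to increase adherence to orthopedic shoes at home after 3 months from 31% (without MI) to 40% (with MI) [11]".
- **MI gain, as assumed:** "we conservatively anticipate that the MI provided by the podiatrists will improve adherence by at least 10%".
- **Digital-fitting gain, as assumed:** "to increase adherence with at least another 10%, due to the experienced improvement of last accuracy and orthopedic shoe-fitting". No source is cited.
- **Control rate:** "Based on the observed 3 months adherence of 59% for the usual care procedure [11]", which the authors expect to fall to a 1-year overall adherence of 40%.
- **Contrast:** 40% plus 10 plus 10, so 40% v 60%.
- **Durability:** the same paragraph says that in the cited study the improved adherence went back to its baseline level over time.
- **Calculation:** "based on a two-sided alpha of 0.05, power of 0.80, and intraclass correlation of 0.01 of patients within podiatrists", giving 200 participants, raised to 220 for loss to follow-up of about 6%.

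The primary outcome is a binary classification of each participant, "defined as minimally 80% of steps taken with orthopedic shoes", based on the mean of two 1-week recordings at T1 and T3. The Discussion moves these recordings to 3 and 6 months. The only percentage in the article worded on that scale is in Background and rationale {6a}: "only 46–49% of patients wearing their orthopedic shoes for at least 80% of daily total steps". The calculation does not use it.

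**The concern.** The MI half of the 20-point effect changes character between its source and its use, in four ways.

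1. **Size.** The source gain is 40 − 31 = 9 points. Entering at least 10 rounds it up, which is the opposite of conservative.
2. **Setting.** The source gain applies at home. The primary outcome counts all steps. The transfer is not stated as an assumption.
3. **Persistence.** The source gain was seen at 3 months, and the paragraph itself says it was lost later. Decline over time is used to lower the control rate from 59% to 40%, but the MI gain is kept in full in a contrast described as 1-year. The primary outcome is measured in neither setting: it averages two recordings within the first half-year or so.
4. **Measure.** Two figures without MI, from the same study at the same 3 months, are 31% and 59%. They are very unlikely to be one measure, and the section does not say what either one counts: mean percentage of steps, or share of participants reaching 80%.

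The effect size is what supports 220 participants and the stated power of 0.80. If the evidence-based half of it is overstated, a null result would be set against a power that the cited evidence does not support.

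**Working it through.** **Inputs.** Two-sided alpha 0.05, power 0.80, ICC 0.01, 200 participants analysed, 220 recruited (Sample size). Clusters: 20 podiatrists (Sequence generation), or 20 + 12 + 16 = 48 after the additions in the Discussion. Evaluable after 6% loss: 220 × 0.94 ≈ 207. Equal arms and equal cluster sizes are assumed.

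**Formulas.** Two proportions, normal approximation, unpooled variance.
- Design effect: DE = 1 + (m − 1) × 0.01, with m = N / number of podiatrists.
- Effective number per arm: n = (N/2) / DE.
- Power = Φ(|p2 − p1| / √(V/n) − 1.96), with V = p1(1 − p1) + p2(1 − p2).

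**Step 1. Reproduce the plan's figure (40% v 60%).** V = 0.24 + 0.24 = 0.48. Per arm without clustering: (1.960 + 0.842)² × 0.48 / 0.20² = 7.849 × 12 = 94.2. With 20 podiatrists and m = 10, DE = 1.09, so the total is 2 × 94.2 × 1.09 = 205, within 3% of the stated 200. Power at 200: n = 100/1.09 = 91.7; SE = √(0.48/91.7) = 0.0723; 0.20/0.0723 = 2.765; Φ(2.765 − 1.960) = 0.79. With 48 podiatrists it is 0.81. The stated figures reproduce.

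**Step 2. Does the control rate matter?** Keep 20 points, with 207 evaluable and 20 or 48 podiatrists:

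| Contrast | Power |
|---|---|
| 31% v 51% | 0.82–0.84 |
| 40% v 60% | 0.80–0.82 |
| 48% v 68% | 0.81–0.83 |

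Between 31% and 48%, the base rate hardly changes the answer.

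**Step 3. Use the source's own MI gain (9 + 10 = 19 points, 40% v 59%).** V = 0.24 + 0.2419 = 0.4819. At N = 200 with 20 podiatrists: SE = √(0.4819/91.7) = 0.0725; 0.19/0.0725 = 2.622; Φ(0.662) = 0.75.

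| N | 20 podiatrists | 48 podiatrists |
|---|---|---|
| 200 | 0.75 | 0.77 |
| 207 | 0.76 | 0.78 |

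The loss against 20 points is about 4 percentage points of power in every cell. A pooled-variance formula gives 0.73 at N = 200 with 20 podiatrists, against 0.78 for 20 points, so the loss is the same.

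**Step 4. Partial transfer (assumption).** The documents give no MI effect on all steps. Suppose half the at-home gain carries over: 4.5 + 10 = 14.5 points, 40% v 54.5%. Power is 0.51–0.53 at N = 200 and 0.52–0.55 at 207. This illustrates how sensitive power is to the transfer and is not an estimate.

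**The case against.** The strongest reply is that nothing was miscalculated. The 40% v 60% contrast enters as two proportions for a binary outcome, and 200 participants do give about 0.80 power for it. Power is always conditional on a postulated effect, and 9 against 10 points costs only about 4 percentage points of power. Recruitment is under way, and the Discussion already concedes that 220 is no longer realistic within the intended period. All of this stands. It limits the size of the point, but it does not make 9 points a conservative basis for 10 or reconcile a full 1-year gain with a reported return to baseline.

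Several stronger readings are tempting and are not supported.

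- **That the gains are added to the 59%.** They are added to an assumed 40%; the 59% is only where the judged drop starts.
- **That the whole 40% v 60% contrast is on the wrong scale.** The measure behind 59% is not named, so this cannot be shown. What can be said is that neither figure is shown to be on the primary scale. The mismatch also reaches only the MI half, since the digital-fitting gain does not come from that study.
- **That the control rate had to be 46–49%.** The plan gives a reason for going lower, namely longer-term decline, and step 2 shows that re-anchoring barely moves power.
- **That power is really 0.24–0.30.** Such values (40% v 49% or 50%) come from setting the digital-fitting gain to zero. That is a separate objection, and the at-home mismatch does not produce it.

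**Conclusion.** The concern holds as a fault in the effect assumption, not in the arithmetic. The Sample size section contradicts its own figures: a 9-point at-home gain at 3 months becomes at least 10 points of overall adherence, is called conservative, and is kept in full in a 1-year contrast although the section reports that the gain was lost. The 31% and 59% figures remain unreconciled.

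On the source's own number, power is about 0.75–0.77 at 200 participants and 0.76–0.78 at 207 evaluable, a modest shortfall from 0.80. It falls further, to about 0.51–0.55, only on the assumption that half the at-home gain transfers. These figures rest on the normal approximation, ICC 0.01, equal arms and clusters, 20 or 48 podiatrists, and the plan's unreferenced 10 points for digital fitting taken as given.

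**What to change.** In the Sample size section:

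1. Delete the word *conservatively* where it introduces the 10% MI gain. Its later use, about aiming for 220, is a separate matter.
2. State the MI gain as 9 points in at-home adherence at 3 months. Label as assumptions both its transfer to all steps and its persistence, given the reported return to baseline.
3. Name the measure behind each cited percentage (31%, 40%, 59%): where it was recorded, and whether it is a mean percentage of steps or a share of participants reaching 80%.
4. Report power of about 0.76–0.78 for 19 points alongside 0.80 for 20 points.

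The cost is a rewritten paragraph and one added power figure. No extra enrolment, data or analysis is needed. The downside is that the stated power becomes slightly less favourable.

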## Discussion

Currently, there is little knowledge about the effectiveness of interventions, and the cost-effectiveness of the novel care approach (motivational interviewing combined with digital shoe-fitting) has not been studied at all [29]. Therefore the aim of this randomized controlled trial is to assess the (cost-)effectiveness of this novel care approach compared to usual care in terms of adherence to wearing orthopedic shoes and ulcer prevention. Since the start of including the first participants in our study, we improved and modified our initial protocol based on operational and logistic issues and new insights; the most important changes are described and explained below.

As in any trial, patient recruitment is crucial. Based on the abovementioned power analysis the required sample size, including the loss to follow-up, for this study was estimated at 220 participants. These participants were to be included in a period of 9 months throughout The Netherlands. However, for practical reasons, it was not feasible to include throughout The Netherlands, and therefore inclusion will only take place in the east of The Netherlands. Because of this change and the outbreak of COVID-19, the goal of 220 participants is no longer realistic with the initially defined criteria and design in the intended period. In order to include as many participants as possible, we were forced to make some changes to the original study protocol.

First, we no longer include only patients receiving their first pair of orthopedic shoes, but we also include patients who already had orthopedic shoes and are eligible for a new pair of orthopedic shoes. Therefore, the pedorthist is now also actively involved in participant recruitment.

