Second, due to this new role of the pedorthist, the background assignment of the treating podiatrist (being trained in MI or not) no longer determines the shoe-fitting procedure by the pedorthist. Each pedorthist has his/her own procedure of shoe-fitting: the new digital shoe-fitting procedure or the casting-based shoe-fitting procedure. In addition, the existing last is also used for an extra pair of orthopedic shoes, and thereby the shoe-fitting procedure is already determined for each subsequent pair of orthopedic shoes. However, the background assignment of the treating podiatrist remains leading over the shoe-fitting procedure with regard to which group the participant belongs to (intervention or control group), because most participants have been treated by the same podiatrist for years and we do not want to change that for this study. The participants in the intervention group will have an appointment with their podiatrist or one of the other MI-trained podiatrists to perform motivational interviewing before or as soon as possible after they receive their first or new pair of orthopedic shoes.

Last, the second group of 12 additional podiatrists received MI training, and 16 podiatrists have been added to the control group to further increase inclusion. Because the inclusion in the intervention group lagged behind the control group, the second group of podiatrists, who received MI training, consists of the podiatrists who see most patients with diabetes. This is in contrast to the original group of podiatrists, who were assigned to one of the groups based on stratified randomization.

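### The stated 80% power assumes shoe-fitting differs fully by arm; the changed design drops that rule and the sample size was not redone

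*Protocol article*

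**What the plan says.** Sample size {14} gives the usual-care rate as follows: "we expect the 1-year overall adherence to drop to 40% for the usual care". It adds two components to reach the intervention rate: "40% + 10% + 10% = 60% for the novel care approach including the MI". For the first component, "we conservatively anticipate that the MI provided by the podiatrists will improve adherence by at least 10" per cent, citing a rise from 31% to 40% in an exploratory study. The second component is a further 10 points or more for digital fitting. The calculation is "based on a two-sided alpha of 0.05, power of 0.80, and intraclass correlation of 0.01 of patients within podiatrists". It yields 200 participants, raised to 220 for loss to follow-up.

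Time point −T1 (inclusion), Sequence generation {16a} and Concealment mechanism {16b} all tie fitting to arm: digital for participants of MI-trained podiatrists, casting for the others.

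The Discussion reports changes made after inclusion began. The podiatrist's assignment "no longer determines the shoe-fitting procedure by the pedorthist". Each pedorthist uses one procedure of his or her own, and an existing last already fixes the procedure for later pairs. A participant's group follows the podiatrist alone. The Discussion still refers back to the same power analysis and its 220, and reports no recalculation.

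**The concern.** The planned 20-point contrast is the sum of two effects, and each must differ between arms to count. MI still does, since it defines the arm. Digital fitting was to differ by rule, and that rule is gone. If both arms contain a mix of digitally fitted and cast shoes, part or all of the second 10 points appears in both arms and cancels in the comparison. The primary analysis is a single mixed model on the arm contrast, so this loss falls directly on the primary test.

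Readers will judge a non-significant result against the stated 80%. If the real figure is well below that, such a result says much less about the novel care approach than the protocol implies.

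**Working it through.** **Inputs.** From Sample size {14}: two-sided alpha 0.05, power 0.80, "intraclass correlation of 0.01 of patients within podiatrists", rates 40% and 60%, N = 200 (220 with loss), loss 10/171 = 5.8%. From Sequence generation {16a}: 20 podiatrists. From the Discussion: 12 + 16 more, so 48. Assumed here: equal arms, equal cluster sizes, and a two-proportion normal approximation with a design effect in place of the mixed model.

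**Formulae.** With m participants per podiatrist, the design effect is DE = 1 + (m − 1) × 0.01. With n per arm, SE = √{[p0(1 − p0) + p1(1 − p1)] × DE / n}. Power = Φ(|p1 − p0| / SE − 1.96).

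**Step 1: the plan's own figure.** N = 200 and 20 podiatrists give m = 10 and DE = 1.09. For 40% v 60%, SE = √(0.48 × 1.09 / 100) = 0.0723, the ratio is 0.20 / 0.0723 = 2.765, and power = Φ(0.805) = 0.79. Solving for power 0.80 gives N of about 206. The number of podiatrists entered in the plan's calculation is not stated, and with 48 podiatrists the same formula gives about 194. The stated 200 therefore reproduces. For loss, 200 / (1 − 10/171) = 212.4, so 213; 220 covers it.

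**Step 2: contrast under the changed design.** Let s1 and s0 be the digitally fitted shares in the intervention and control arms. On the plan's own component effects:

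- control rate = 40 + 10 × s0
- intervention rate = 40 + 10 + 10 × s1
- contrast = 10 + 10 × (s1 − s0)

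The plan's 20 points is the case s1 = 1, s0 = 0. The documents give neither share.

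**Step 3: power by difference in digital share.** Evaluable N = 220 × (1 − 10/171) = 207. With 48 podiatrists, m = 207/48 = 4.31 and DE = 1.033. The shares are placed symmetrically (s1 + s0 = 1); this choice hardly affects the result.

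| s1 − s0 | Rates (control v intervention) | Contrast | Power |
|---|---|---|---|
| 0 | 45% v 55% | 10 points | 0.30 |
| 0.25 | 43.75% v 56.25% | 12.5 points | 0.43 |
| 0.5 | 42.5% v 57.5% | 15 points | 0.57 |
| 0.75 | 41.25% v 58.75% | 17.5 points | 0.71 |
| 1 | 40% v 60% | 20 points | 0.82 |

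Worked row for a difference of 0: SE = √(0.495 × 1.033 / 103.5) = 0.0703, the ratio is 0.10 / 0.0703 = 1.423, and power = Φ(−0.537) = 0.30. Taking 40% v 50% instead also gives 0.30.

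**Step 4: minimum detectable difference.** From a control rate of 40%, with N = 200 and power 0.80, it is about 20 points (19.8 with 48 podiatrists, 20.3 with 20). The design has almost no margin below the full 20.

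**Step 5: two lesser points in the same section.**

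- The cited gain is 40 − 31 = 9 points, so an assumption of at least 10 is above its source and is not conservative. If 9 replaces 10 and fitting is balanced across arms, 40% v 49% gives power 0.25.
- The rates are labelled 1-year overall. The primary outcome (Proportion participants being adherent) averages two activity weeks, which the Discussion now places at 3 and 6 months after the shoes are received.

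**The case against.** The strongest objection is that the Discussion says only that assignment has stopped determining fitting. It does not say that the two are now unrelated. Participants enrolled before the change may have been fitted by arm, and alignment through pedorthist or location may persist. This stands. A reader might infer that the contrast has fallen to 9 or 10 points and power to 25–30%. That is the case of no remaining link, and the documents do not state it. It is the lower end of a range.

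It can also be said that the calculation was correct when made. That stands too: Step 1 reproduces it.

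Three further inferences are tempting and should not be drawn.

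- *That 220 has been given up.* The Discussion says "the goal of 220 participants is no longer realistic", but qualifies this by the initial criteria, design and period, and then describes changes meant to raise inclusion. A smaller N is a risk, and no revised target is given.
- *That the MI effect should be taken as lost.* The section does say of the source study that "over time the improved adherence returned to baseline levels". However, the cited gain is itself a 3-month gain, the outcome weeks are now at 3 and 6 months, and MI is repeated at later consultations. The documents do not say when the gain faded.
- *That 9 points is the right MI input.* The source figure is adherence at home. The documents do not show that it is the proportion of participants reaching 80% of all steps.

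None of this restores the 80%. Even a share difference of 0.75 leaves 0.71.

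**Conclusion.** The point holds in limited form. The 80% power follows only from complete separation of fitting method by arm, and the current design no longer secures that. On the plan's own component effects, the contrast is an assumption lying between 10 and just under 20 points. Power lies between about 0.30 and just under 0.82 at 207 evaluable participants. This rests on 48 podiatrists in balanced arms, an intraclass correlation of 0.01, additive 10-point components and a normal approximation to the mixed model. Where the trial sits in that range cannot be determined from the documents, because neither the fitting split by arm nor the number enrolled before the change is given. The fault is an input left unrevised after a design change. The claim to be conservative and the 1-year label are minor errors beside it.

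**What to change.** Restate Sample size {14} for the trial as now run:

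- report the digital and casting shares by arm, or a stated range if they are not yet known;
- give the expected contrast as 10 + 10 × the difference in shares, with power at the realised N as a range;
- give the minimum detectable difference, about 20 points at N = 200;
- remove the word conservatively, or use the 9 points of the source;
- replace the 1-year label with the time frame of the 3- and 6-month outcome.

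Time point −T1, Sequence generation {16a}, Concealment mechanism {16b} and Sample size {14} must also be reconciled with the Discussion on whether arm determines fitting. The cost is a paragraph of text, a count of fitting method by arm, and a less favourable stated power. No extra enrolment and no change to care is proposed.
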